### Study objectives

Given the gap in the current literature and the need to address circadian-related factors in youths with insomnia, this study aims to examine the efficacy of CBT-I and CBT-I plus bright light therapy in reducing insomnia severity in adolescents compared with a waitlist control. The secondary aim of the study is to examine the effects of CBT-I and CBT-I plus bright light therapy on mood symptoms and daytime functioning (e.g. sleepiness, fatigue, cognitive performance), as well as subjective and objective sleep and circadian measures.

The primary hypotheses for the trial are as follows:Both CBT-I and CBT-I plus BLT will lead to an improvement in self-reported insomnia symptoms by the end of treatment as compared to the waitlist control.CBT-I plus BLT will additionally lead to an advancement of chronotype and sleep onset by the end of treatment compared to the waitlist control.Changes in insomnia will mediate the changes in mood and other daytime symptoms.

The secondary hypotheses are as follows:CBT-I and CBT-I plus BLT will improve objectively measured sleep outcomes, mood symptoms, daytime functioning, and insomnia-related behaviours and cognitions by the end of treatment compared to the waitlist control.The treatment effects of CBT-I and CBT-I plus BLT will be maintained over time at 1 month and 6 months after treatment.

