### Measures

#### Primary outcomes

The primary outcome is the change in insomnia symptoms as measured by the Insomnia Severity Index (ISI). The ISI is a seven-item self-rated scale designed to measure one’s insomnia problems, satisfaction with sleep, noticeability and worries towards one’s sleep problems, and insomnia-related interference with daily life. The possible score ranges from 0 to 28, where a higher score indicates greater insomnia severity. The ISI has been validated in local youths demonstrating good construct validity and high internal consistency with a Cronbach’s alpha of 0.83 [40].

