### Statistical analysis

#### Sample size estimation

The target sample size was estimated based on the primary hypothesis using a priori power analysis. We expected a medium effect size (Hedges’ *g* = 0.30–0.47) based on the previous research [33]. Using *g* = 0.30 as a more conservative effect size, a total of 111 participants was estimated assuming a significance of 0.05 and an 80% power. Accounting for a 30% anticipated attrition rate, the final target sample size for the overall trial was 144 (*n* = 48 per arm).

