#### Main analysis

The main analyses will be conducted following the intention-to-treat principle. Multilevel modelling (MLM) with restricted maximum likelihood estimation and an unstructured variance–covariance matrix will be used to analyse the main hypotheses on outcome measures. The use of MLM in analysing RCT data has the advantage of accounting for individual differences as a random effect [67–69]. MLM also has advantages over the traditional general linear model approach (e.g. mixed model repeated measures ANOVA) as it is unaffected by randomly missing data and can handle both time-dependent and independent covariates [67, 69]. Missing data for dependent variables will be assumed to be missing at random and accounted for by the maximum likelihood estimation. Two sets of MLMs will be conducted; one will include three treatment arms (CBTI + BLT vs CBTI-BLT vs WL) and two timepoints (pre-treatment vs post-treatment) as fixed effects; the second set will consist of two treatment arms (CBTI + BLT vs CBTI-BLT) and four timepoints (pre-treatment vs post-treatment vs 1-month follow-up vs 6-month follow-up) as fixed effects. The treatment × time interaction will also be included as a fixed effect on both MLMs and will be considered the treatment effect, while repeated measures will be nested within individual participants as random intercepts. A *p*-value of 0.05 represents statistical significance in all analyses. The *p*-values on outcome measures will be adjusted using the Benjamini–Hochberg procedure with a false discovery rate set as 20% to account for multiple comparisons.

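### The plan sets both p = 0.05 and a 20% false discovery rate, does not say which decides the primary outcome ISI, and so does not secure a 5% error rate for it

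*Protocol article*

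**What the plan says.** There is one primary outcome: "The primary outcome is the change in insomnia symptoms as measured by the Insomnia Severity Index (ISI"). The Main analysis section ends with two adjacent statements on significance. The first is that a p-"value of 0.05 represents statistical significance in all analyses". The second is that the p-values on outcome measures are adjusted by the Benjamini–Hochberg "procedure with a false discovery rate set as 20% to account for multiple comparisons".

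Nothing in the article exempts ISI from the second statement, defines the family of tests, or says which statement settles whether a result is positive.

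The Sample size estimation section works at the 5% level: it takes "0.30 as a more conservative effect size, a total of 111 participants was estimated assuming a significance of 0.05 and an 80% power".

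**The concern.** BH at a 20% false discovery rate is a decision rule in its own right. It can reject hypotheses whose raw p-value is above 0.05, and it can refuse to reject hypotheses whose raw p-value is below 0.05. Placed next to a blanket 0.05 rule, it leaves more than one possible verdict on the same ISI result.

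Two things are at stake. First, if ISI is adjusted together with other outcomes, its cut-off depends on how many of them succeed, so the primary claim no longer rests on the primary data alone. Second, the 80% power was planned at 0.05 and need not apply under the rule finally used. A choice between 0.05 and 20% made after results are seen would depend on the data.

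**Working it through.** **1. The plan's own figure uses 0.05.** Take a treatment × time F test with three arms and two timepoints, f = 0.30/2 = 0.15 and an assumed pre–post correlation of 0.5. The noncentrality is f² × N × 2/(1 − 0.5) = 0.0225 × 111 × 4 = 9.99. With 2 and 108 degrees of freedom and alpha 0.05, power is 0.803, so N = 111 is reproduced. A one-way three-group ANOVA with f = 0.30 has the same noncentrality (0.09 × 111 = 9.99) and also gives 0.803. The final 144 is 111 × 1.3 = 144.3. Both routes to 111 use alpha = 0.05.

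**2. Number of tests (each scale and task counted once, an assumption).**
- ISI: 1
- Secondary scales (PSQI, MCTQ, CDRS, HADS, DSI-SS, PDSS, MFI, KIDSCREEN-27, Clinical Global Impression): 9
- Diary and actigraphy sleep parameters: 7 + 7
- Actigraphy circadian parameters: 3 + 5
- Neurocognitive tasks: 8

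The total is 40 for the three-arm model. The 5 polysomnography outcomes and 1 melatonin-onset outcome would make 46, but Other secondary measures limits them to half of the two treatment arms, so they cannot enter a comparison with waitlist.

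**3. ISI cut-off if BH at 20% decides and ISI is pooled.** With k of m tests rejected, the cut-off is q × k/m. For q = 0.20 and m = 40 this is 0.005 × k:
- k = 1: 0.005
- k = 10: 0.05
- k = 40: 0.20

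It exceeds 0.05 once more than 0.05/0.20 = 25% of the family is rejected.

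**4. Error rate of ISI when ISI is truly null.** This is by simulation of BH at q = 0.20, with two-sided normal tests and real secondary effects shifted by 2.8 standard errors (about 80% power each at 0.05). Entries are the percentage of trials in which ISI is falsely declared positive.

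| Tests, correlation | 0% of secondary effects real | 25% | 50% | 75% | 100% |
|---|---|---|---|---|---|
| 10, independent | 3.0 | 6.5 | 10.3 | 15.5 | 18.8 |
| 40, independent | under 1 | about 5 | about 10 | about 15 | 18–19 |
| 46, independent | 0.7 | 5.0 | 9.9 | 14.9 | 18.5 |
| 46, correlation 0.4 | 2.3 | 5.7 | 9.5 | 13.7 | 17.6 |

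The share of real effects drives the result. The family size matters mainly at the low end.

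**5. Power of ISI, planned at 80%.** With 40 independent tests it runs from about 54% (no secondary effect real) to about 93% (all real). With 46 tests it runs from about 51–52% to 91–93% across the two correlations.

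**6. The smallest plausible family: two ISI contrasts with waitlist.** BH at 20% rejects something if either p ≤ 0.10 or both p ≤ 0.20. With both contrasts null and independent, the probability is (1 − 0.9²) + 0.1² = 0.19 + 0.01 = 0.20. Sharing the waitlist arm correlates the contrasts and lowers this slightly.

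**7. Readings that would protect ISI.** Requiring raw p ≤ 0.05 as well as BH at 20% keeps the ISI error at about 5% or less in every scenario above. Comparing the BH-adjusted p-value with 0.05 keeps it at about 4% or less, but the false discovery rate is then 5%, not the stated 20%.

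**The case against.** The strongest reply is that the two statements can be read together, with 0.05 as the cut-off and BH as an extra filter. Step 7 shows that ISI would then stay near or below 5%. This is a fair reading, so the statements are not logically irreconcilable. But the article states no joint rule, and the reading has to be supplied by the reader.

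Several stronger inferences are tempting and should not be drawn.

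- **That ISI definitely shares one family with dozens of outcomes.** The article speaks only of outcome measures. BH might run by model, by domain or across contrasts, and such detail is commonly left to an analysis plan. The point does not need a single large family, as step 6 shows.
- **That the ISI error rate is simply 15% or more, or that a raw p near 0.20 will pass.** The rate exceeds 5% only when more than about a quarter of secondary effects are real. A cut-off near 0.20 needs almost every outcome rejected. A null ISI beside mostly real mood and daytime effects also fits poorly with the trial's own hypothesis that insomnia changes mediate those effects.
- **That any significance claim at 0.05 would be false.** This holds only if BH at 20% alone decides.
- **That the interaction test or the hypothesis labels are part of the same error.** The primary hypotheses include that "CBT-I plus BLT will additionally lead to an advancement of chronotype and sleep onset by the end of treatment compared to the waitlist control", while chronotype and sleep onset are listed as secondary outcomes. That mismatch deserves tidying but is separate. The interaction being named as the treatment effect does not exclude arm-specific contrasts.

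Nor is a 20% rate for secondary outcomes wrong in itself. It is a choice the trial may make if it is labelled for what it is.

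**Conclusion.** The point stands as a defect in a stated rule, not as missing detail. The article fixes 0.05 for all analyses, fixes 20% for outcome measures, leaves ISI inside the second statement, and sizes the trial on 0.05. An analysis plan could settle this only by overriding or qualifying what is printed.

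On the reading that BH at 20% decides and ISI is pooled, the ISI type I error lies anywhere from under 1% to about 18–19%, and its power from about 54% to 93% against the planned 80%. This rests on the inferred pooling, the count of about 40 tests, independence, about 80% power per real effect, and an unknown share of real secondary effects (hence the full range). With two ISI contrasts alone, the chance of a false ISI claim is about 20% if both are null and independent. Only rules that the article does not state hold ISI near 5%.

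**What to change.** Before outcome data are analysed:

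- Exclude ISI from the BH procedure and test it at two-sided 0.05.
- Name the test that carries this level: the two post-treatment ISI contrasts, CBTI + BLT versus waitlist and CBTI-BLT versus waitlist. Test each at 0.05 if both must succeed, as hypothesis 1 is worded, or use Holm if one suffices. Testing each at 0.05 and claiming success on either would allow up to 1 − 0.95² = 9.75% under independence.
- Limit the 20% false discovery rate to the secondary outcomes and label those findings exploratory.
- Delete the statement that 0.05 applies in all analyses.

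The change is one of wording and matches the 0.05 already used for the sample size, but it has costs. Secondary results carry a weaker claim. ISI loses any looser threshold that BH at 20% would have given it. Requiring both contrasts has less power than one overall interaction test, which is the kind of test that reproduces N = 111. For scale, if g = 0.30 is taken as a pairwise difference (the article does not say), an unadjusted two-sample t-test with 111/3 = 37 per arm has about 25% power per contrast and about 12% for both. Baseline adjustment would raise this.

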#### Other analysis

For analysing the mediating effect of insomnia on the changes in mood and other daytime symptoms, the mediator (i.e. insomnia) will be added to the multilevel models for each of the primary and secondary outcomes (described above). An interim analysis is planned to be conducted when more than half of the participants have completed the 6-month follow-up assessment. The principal investigator (PI; [name]) is responsible for reviewing the interim analysis results for efficacy and futility purposes.

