### Procedures

Interested individuals can register for the study using an online application form and will be initially screened based on age, ISI score ≥ 9, and rMEQ score ≤ 11. Potential eligible individuals will then be invited to attend a face-to-face clinical interview to ascertain their eligibility for the trial. The diagnoses of sleep disorders and psychiatric disorders will be ascertained using the Diagnostic Interview for Sleep Patterns and Disorders [42] and the Mini International Neuropsychological Interview, respectively [43]. After confirming their eligibility, participants will be randomised to one of the following groups: CBTI + BLT, CBTI-BLT, and WL. Assessments are scheduled at pre-treatment (Week 0), during treatment (Week 2 and Week 4), and post-treatment (Week 7). Assessments at Week 2 and Week 4 will consist of two self-report measures (Insomnia Severity Index and Hospital Anxiety and Depression Scale) for monitoring the clinical status of the participants. Actigraphy will also be used in Week 4 to objectively monitor sleep and circadian-related changes and light exposure across the groups. The two active intervention arms (CBTI + BLT and CBTI-BLT) will be additionally followed up at 1 month and 6 months after the conclusion of the last group session. Participants in the WL group will be offered the treatment (either CBTI + BLT or CBTI-BLT) after completing the post-wait assessment. Figure 1 shows the study flowchart, and the study schedule is summarised in Table 1. Participants will receive HKD 500 (~ USD 64) at the end of the follow-up period as a token of appreciation of their participation in this trial.

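### The stated mediation step for primary hypothesis 3 includes the ISI model itself and, in the waitlist comparison, has an effect only with same-visit insomnia values, which cannot show direction

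*Protocol article*

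**What the plan says.** Under Study objectives, the third primary hypothesis is "Changes in insomnia will mediate the changes in mood and other daytime symptoms". The method is in Other analysis, where one sentence gives the purpose, "For analysing the mediating effect of insomnia on the changes in mood and other daytime symptoms", and then the step: "the mediator (i.e. insomnia) will be added to the multilevel models for each of the primary and secondary outcomes". The sentence points back to the models already described.

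Primary outcomes gives only one such outcome: "The primary outcome is the change in insomnia symptoms as measured by the Insomnia Severity Index (ISI".

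Main analysis describes two sets of multilevel models. The first has "three treatment arms (CBTI + BLT vs CBTI-BLT vs WL) and two timepoints (pre-treatment vs post-treatment) as fixed effects". For the other, "the second set will consist of two treatment arms (CBTI + BLT vs CBTI-BLT) and four timepoints", namely pre-treatment, post-treatment, 1 month and 6 months. The treatment-by-time "interaction will also be included as a fixed effect on both MLMs and will be considered the treatment effect".

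Procedures adds mid-treatment data that neither set of models uses: "Assessments at Week 2 and Week 4 will consist of two self-report measures (Insomnia Severity Index and Hospital Anxiety and Depression Scale". The article does not say whether the mediator enters as a same-visit, lagged, mid-treatment or change value.

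**The concern.** There are two problems. First, the list of models that receive the mediator is wider than the purpose given in the same sentence. It takes in the primary outcome, which is the mediator.

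Second, the step is to add a term to existing models. The only model that compares treatment with waitlist has one visit before and one after treatment. If insomnia enters at those visits, mediator and outcome are measured together. A smaller treatment effect after adjustment could then mean that insomnia drives mood, that mood drives insomnia, or that something else drives both.

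The hypothesis is listed as primary. A reader of the results could take a shrunken treatment effect as support for a causal pathway that the analysis cannot single out.

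**Working it through.** The plan states no figure for this point, so there is none to reproduce. All effect sizes below are assumed for illustration; only the model structure and the 48 per arm come from the article.

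**1. Insomnia in the ISI model.** Regress ISI on arm, time, arm-by-time and same-visit ISI. The ISI coefficient is 1, every other coefficient including arm-by-time is 0, and the residual sum of squares is about 6e-29. The treatment effect vanishes by construction.

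**2. What an added term can do in the pre/post model.** Let T be treatment and X a person-level covariate such as Week 4 ISI or an ISI change score.

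- Pre: Y0 = α + βT + θX + error
- Post: Y1 = α + τ + (β + δ)T + θX + error
- Difference: Y1 − Y0 = τ + δT + error

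X cancels. With complete data, δ (treatment-by-time) is the difference in mean change whether or not X is added. In simulated complete data with 48 per arm and a random-intercept REML model, δ was −0.596 both before and after adding Week 4 ISI or an ISI change score.

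If the mediator M is instead taken at each visit, the difference becomes Y1 − Y0 = τ + δT + b(M1 − M0) + error, and δ can move. In the same data it went to −0.326. So in this model the stated step either uses same-visit insomnia or does nothing to the treatment effect.

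**3. What same-visit adjustment shows.** Write a for the treatment effect on insomnia, c for the total effect on mood, b for the insomnia coefficient in the mood model, and c′ for the treatment effect after adjustment. Then c′ = c − b × a.

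Large-sample arithmetic, in SD units as magnitudes, with no effect of insomnia on mood:

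- Mood drives insomnia: treatment moves mood by 0.5 and the mood-to-insomnia correlation is 0.5, so a = 0.5 × 0.5 = 0.25 and b = 0.5. c′ = 0.5 − 0.5 × 0.25 = 0.375, a 25% reduction (0.125/0.5).
- Shared cause: a = 0.8, c = 0.4, residual correlation 0.5, so b = 0.5. c′ = 0.4 − 0.5 × 0.8 = 0, a 100% reduction. These inputs were chosen to reach zero.

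Simulation with other assumed effects (random-intercept REML, pre/post, 48 per arm, two active arms pooled against waitlist, 200 replicates; percentages from unrounded values):

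| True structure | a | b | c | c′ | Reduction | b significant |
|---|---|---|---|---|---|---|
| Insomnia drives mood | −0.98 | 0.49 | −0.50 | −0.02 | 97% | 100% |
| Mood drives insomnia | −0.51 | 0.44 | −1.00 | −0.78 | 22% | 100% |
| Shared cause | −1.01 | 0.48 | −0.71 | −0.22 | 69% | 100% |

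The mediator was significant in every replicate of all three structures, and c′ was smaller than c in all three. If a = 0, then c′ = c, so correlation between ISI and mood alone produces no apparent mediation. A treatment effect on ISI, which the first primary hypothesis expects, is also needed.

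**4. The four-timepoint model.** Its visits would allow insomnia at one visit to precede mood at the next. But it holds only the two active arms, both of which receive CBT-I, so it cannot address mediation of the effect against waitlist.

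**5. Data already planned.** ISI and HADS are collected at Weeks 2 and 4, before the Week 7 post-treatment visit. Week 4 ISI could therefore be placed ahead of the Week 7 outcomes.

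**The case against.** The strongest reply is that the ISI-on-ISI model is a drafting slip. The same sentence and the hypothesis both limit the purpose to mood and daytime symptoms, and removing the primary outcome from the list cures it. That is fair as to intent, but the text as published still states the wrong list.

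A reader might infer that the analysis cannot test hypothesis 3 at all. The document does not support that. The main ISI model gives a, and the mood model with ISI added gives b and c′, so a product-of-coefficients assessment is possible. Its weakness is temporal order. Nor does the plan say that the mediator is concurrent, or that all its models stop at post-treatment: same-visit timing is an inference for the three-arm model, and the second set has four timepoints.

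It is also tempting to object that no indirect effect or confidence interval is named. A condensed article may leave that to a fuller plan, so the omission carries no weight here.

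The remedy has limits too. Week 4 ISI does not remove an unmeasured common cause, and Week 4 falls within a six-session weekly programme, so later change is missed. Only ISI and HADS are self-reported mid-treatment, so sleepiness, fatigue and clinician-rated depression have no Week 4 values for a reverse model. Table 1 marks the waitlist row only at pre- and post-treatment, and Procedures does not settle whether that arm completes the Week 2 and Week 4 questionnaires. All of these points stand and shape the fix.

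**Conclusion.** The point holds in two parts. On its wording, the plan enters insomnia into the model for insomnia, which is degenerate and contradicts the stated purpose. This rests on the text alone.

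In the only model with a waitlist comparison, the stated step can alter the treatment effect only through same-visit insomnia values. This rests on complete data and on the mediator being added as a single term without its own interaction with time. With same-visit values and a treatment effect on ISI, mediation cannot be separated from reverse or shared causation. The size of the false signal depends wholly on assumed inputs: 22% and 25% in the two reverse-causation examples, 69% and 100% in the two shared-cause examples, the last by choice of inputs.

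It does not follow that hypothesis 3 is untestable, or that any correlation between ISI and mood would confirm it. The planned ISI and HADS collection at Weeks 2 and 4 makes a better-ordered analysis inexpensive, so the paragraph should be changed.

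**What to change.** Rewrite the mediation paragraph as follows.

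- Restrict the mediation models to mood and daytime outcomes, and remove the ISI from the list.
- Confirm that the waitlist arm completes the Week 2 and Week 4 questionnaires. If it does, use Week 4 ISI as mediator of the Week 7 outcome, adjusted for baseline ISI and the baseline value of that outcome.
- Estimate the indirect effect (a × b) with an interval, for example by bootstrap.
- For HADS only, run the reverse model, with Week 4 HADS as mediator of Week 7 ISI, and report it alongside.
- State that the result is not proof of causation, because the mediator is not randomised and unmeasured common causes remain.

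The cost is one rewritten paragraph and a little more analysis, with no new data if the waitlist arm completes the mid-treatment questionnaires. The price is a weaker stated conclusion for hypothesis 3, and change in insomnia after Week 4 is not captured.

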### Monitoring and responsibilities

This is an investigator-initiated clinical trial. The funder did not play any role in the conceptualisation and design of the study and collection, analysis, and interpretation of data and in writing the manuscript. The trial steering team comprising the PI ([name]) and two site-investigators ([name], [name]) will oversee and monitor the entire study process and are responsible for providing supervision and organisational support to the implementation of the trial. The trial implementation team, comprising research assistants and clinical psychologists, will be responsible for the day-to-day support of the trial. In addition, the PI will have bi-weekly meetings with teams at both sites to address any issues during the trial. Due to the non-invasive, non-pharmacological, and low-risk nature of the intervention, a data monitoring committee will not be assembled for this trial. Instead, data monitoring will be conducted by the trial steering team, which will hold monthly meetings with the trial implementation team to review trial progress and adherence to the study protocol.

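### The interim look for efficacy and futility goes to the principal investigator with 0.05 kept for all analyses, and its 6-month trigger does not fit a primary comparison that ends at Week 7

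*Protocol article*

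**What the plan says.** Other analysis sets the timing: "An interim analysis is planned to be conducted when more than half of the participants have completed the 6-month follow-up assessment". It then says that the principal investigator "is responsible for reviewing the interim analysis results for efficacy and futility purposes".

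Main analysis states that a p-value "of 0.05 represents statistical significance in all analyses". Its one multiplicity step is that p-values on outcome measures are "adjusted using the Benjamini–Hochberg procedure with a false discovery rate set as 20% to account for multiple comparisons".

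Under Procedures, the two active arms "will be additionally followed up at 1 month and 6 months after the conclusion of the last group session". Waitlist participants are offered treatment after the post-wait assessment, and Table 1 gives them no 6-month visit. The first primary hypothesis (Study objectives) compares insomnia symptoms with waitlist at the end of treatment, which Procedures places at Week 7.

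Monitoring and responsibilities states that "a data monitoring committee will not be assembled for this trial", citing the low risk of the intervention. The principal investigator sits on the steering team and meets the teams at both sites every two weeks. Data management and dissemination makes the principal investigator and a doctoral student responsible for storing and analysing the data.

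**The concern.** There are three linked problems.

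1. **Error rate.** An efficacy look is an extra chance to declare success. The article keeps 0.05 everywhere, and its false discovery rate step handles several outcomes at one time, not one outcome at several times.
2. **Confidentiality.** Judging efficacy or futility normally requires results by arm. The person named to do it also steers the trial, meets the delivery teams and shares the analysis. Randomisation and masking blinds therapists and assessors, and some outcomes are clinician-rated, so knowledge of interim differences should be kept away from those teams. The low-risk reason for having no committee concerns safety and does not cover efficacy decisions.
3. **Clock.** A trigger based on 6-month completion does not track information on a comparison that is complete at Week 7. It fires when most of the primary data are already in, so stopping can spare little exposure on the primary question. It is also unclear whether half means half of everyone randomised or half of those who have the visit.

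**Working it through.** **Inputs.** Target 144, 48 per arm; 111 before attrition; 30% attrition with no timepoint given (Sample size estimation). 150 participants (Abstract). Allocation 1:1:1. 6-month visit in the active arms only (Procedures, Table 1). Significance 0.05, taken as two-sided because the article does not say.

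**The plan's own figure.** 111 × 1.3 = 144.3, which gives the stated 144. The attrition that 144 actually absorbs is therefore 1 − 111/144 = 22.9%, not 30%. Both rates are used below.

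**Type I error with 0.05 at both looks.** Let t be the share of Week 7 ISI information available at the interim. Under the null hypothesis the two test statistics are bivariate normal with correlation √t, and

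overall error = 1 − P(|Z₁| ≤ 1.96 and |Z₂| ≤ 1.96).

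| t | Overall error |
|---|---|
| 0.50 | 8.3% |
| 0.75 | 7.3% |
| 0.90 | 6.5% |
| 0.95 | 6.0% |

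The article does not give t. Week 7 data accrue about six months ahead of 6-month data, so t should be well above one half when the trigger fires. If only the active arms count, the trigger needs 49 completers. At 30% attrition that is already 49/67.2 = 73% of those expected, before adding participants who have passed Week 7 but not yet six months.

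**Can the trigger be met?** Active participants: 144 × 2/3 = 96, or 150 × 2/3 = 100.

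| Denominator | Attrition by 6 months | Needed | Expected |
|---|---|---|---|
| All 144 | 30% | 73 | 96 × 0.70 = 67.2 |
| All 150 | 30% | 76 | 100 × 0.70 = 70 |
| All 144 | 22.9% | 73 | 96 × 111/144 = 74 |
| Active 96 | 30% | 49 | 67.2 |
| Active 100 | 30% | 51 | 70 |

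If 30% is treated as a per-person probability, the chance of at least 73 completers among 96 is 0.12. With all 144 counted, the break-even is 23 of 96 lost, about 24%. At 22.9%, the 73rd completer is almost the last of the 74 expected, so the look would hardly be interim.

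**Timing.** Trial status expects data collection to finish by the end of December 2023. If that includes the last 6-month visits, active-arm Week 7 data were complete around July 2023, before the protocol version date of 26 September 2023.

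**The case against.** The strongest reply is that the article states no rejection threshold and no stopping rule for the look. Boundaries are commonly left to an analysis plan, which is not shown, and the sentence on 0.05 may be only a general convention. This stands in part: the documents do not show that error is certainly spent twice. But efficacy is named as a purpose, 0.05 is fixed for all analyses, and a separate boundary with a lower final level would contradict that sentence. A look for futility alone would not inflate the error.

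A second reply is that a single test at 0.05 is not the plan's whole decision rule, because the false discovery rate step follows. That is fair. The percentages above describe one comparison tested at 0.05 at each look, not the error rate of the complete plan.

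Two stronger readings are tempting. A reader might infer that the trigger can never be reached. That needs waitlist members in the denominator and the full 30% lost by six months. Even then there is about a 12% chance of reaching it, and on the active-arm count it is readily met. A reader might also take 8.3% as the size of the problem. That figure assumes half the information, which sits badly with a trigger that fires after most Week 7 data are in.

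A third reply is that so late a look can hardly affect recruitment or group delivery. This largely stands. Influence on later analysis choices is the more plausible risk. The article also does not say that interim results will be shown by arm; that is inferred from the stated purpose.

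**Conclusion.** The point holds in limited form. The article assigns an efficacy and futility review to a non-independent reviewer, with no allowance for the extra look. Naming the principal investigator is a stated choice rather than an omission, and that part needs no calculation.

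If the look is used to claim efficacy at 0.05, the excess error on the Week 7 ISI comparison is about 1.0 to 1.5 percentage points when 90 to 95% of Week 7 data are in, 2.3 at three quarters and 3.3 at half. This rests on two-sided tests and an assumed information fraction.

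The trigger is mismatched to the primary endpoint, and its denominator needs defining. It is not expected to be met if everyone randomised is counted and 30% are lost by six months, but the documents do not support calling it unreachable. Nor do they show that a look has been taken.

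**What to change.** - **Preferred:** delete the efficacy and futility purpose. Keep only pooled, blinded monitoring of recruitment, attrition and safety. This is a wording change and loses little, since most Week 7 data precede the trigger.
- **If an efficacy look is kept:** define it by the number of participants with Week 7 ISI, stating which arms are counted. Apply an alpha-spending boundary at the actual information fraction, so that the final level falls below 0.05, and amend the Main analysis sentence to match. Have the results reviewed by someone outside the trial team. A boundary written for half the information may no longer be usable on the stated timeline. The cost is one outside reviewer and a slightly stricter final test.
- **If a look has already been taken:** report when it was taken and which roles saw it, and adjust the final level.
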